### Sample size calculation

We assumed for sample size calculation that effective postoperative rehabilitation could restore the quality of life to a similar level before surgery. A previous lung cancer study showed that the preoperative and postoperative EQ-5D indices were 0.81 ± 0.19 and 0.74 ± 0.11, respectively [20]. Additionally, a minimal clinically important difference in EQ-5D has been observed between 0.03 and 0.05 [21]. Because patients were classified into four groups, the margin of type 1 error was set at 0.008. Calculations showed that a minimum of 76 patients in each group was required to detect a significant difference at the 0.008 level with a power of 0.9 and a dropout rate of 25%.

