### Statistical analysis

SAS (SAS Institute Inc., Cary, NC) and R (version 4.1.2; R Development Core Team, Vienna, Austria) software will be used for all statistical analyses. Continuous variables will be presented as means ± standard deviations or median [interquartile range] and compared by Student’s *t*-test or the Mann–Whitney U-test. Categorical variables will be presented as numbers and percentages and compared by the χ^2^ test or Fisher’s exact test. All tests of significance will be two-sided, with *P* < 0.05 defined as statistically significant.

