## Discussion

Improvements in exercise capacity and quality of life have been associated with more favorable outcomes in patients with lung cancer [22–24]. Recent advances in digital health care have included smartphone application based pulmonary rehabilitation, which is effective in improving exercise capacity and symptoms in patients with advanced lung cancer [25]. This study is designed to expand the therapeutic potential of smartphone application based pulmonary rehabilitation to patients with early-stage lung cancer who are scheduled to undergo thoracoscopic lung resection and will have reduced lung function and volume after surgery. Although this type of clinical trial is currently uncommon, these trials will likely be more common in the near future, as these interventions can overcome the limitations of medical care within a hospital. This study is designed not only to evaluate the efficacy of smartphone application, but also to compare the efficacy of three different  types of smartphone applications. Patients with early-stage lung cancer usually undergo surgery with curative intent, making management that facilitates prompt recovery more important.

Due to the scarcity of medical resources, most clinicians are interested in acute phase treatment. However, sustainable health care management, such as lifestyle modifications outside the hospital, is also important. Digital intervention can be effective in optimizing patient management. Smartphone applications have several advantages, including their relatively high adherence rates compared with other system. The rates of adherence for weight loss was 93% for smartphone applications, compared with 55% for websites and 53% for diaries [26]. In addition, subjects can monitor their step counts and intensity of walking just by carrying a smartphone [27]. Smartphone applications also allow feedback on a patient's lifestyle, thereby motivating patients [18]. Other advantages of digital interventions using smartphone applications include relatively low medical costs and newly developed expandability [18].

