In conclusion, this randomized controlled study is designed to assess the efficacy of smartphone healthcare applications for patients who have undergone thoracoscopic lung resection. In addition, this study will investigate the differences in efficacy among the three applications. Because these applications act via different mechanisms, they may identify the optimal application for patients with lung cancer. This study will likely provide evidence about the efficacy of smartphone healthcare application for digital lifestyle management and improvements in quality of life and exercise capacity via publication. The results of this study may expand the use of digital healthcare application to patients with other types of cancer.

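### The trial is sized at 0.008 but tested at 0.05, and no EQ-5D contrast is named as deciding efficacy; one step-down rule over the six pairs would settle the level and recover some power

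*Protocol article*

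**What the plan says.** All references are to the protocol article.

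- **Sample size calculation.** "Because patients were classified into four groups, the margin of type 1 error was set at 0.008". The inputs are that "preoperative and postoperative EQ-5D indices were 0.81 ± 0.19 and 0.74 ± 0.11", and the result is that "a minimum of 76 patients in each group was required", with power 0.9 and 25% dropout. The reasoning is that effective rehabilitation brings quality of life back to its level before surgery, so the effect is 0.81 − 0.74 = 0.07.
- **Statistical analysis.** "All tests of significance will be two-sided", with P "< 0.05 defined as statistically significant". The methods listed for continuous variables are two-sample tests. The 0.008 level does not reappear, and no adjustment is mentioned.
- **Data collection and study outcome.** The EQ-5D index is the primary endpoint. No contrast between groups is attached to it.
- **Discussion.** The trial is "designed not only to evaluate the efficacy of smartphone application, but also to compare the efficacy of three different" types of application. The conclusion adds: "In addition, this study will investigate the differences in efficacy among the three applications".

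**The concern.** The article fixes two different error levels for the same primary comparison and does not say which one decides. It also has two kinds of question, app versus control and app versus app, and no statement of which result would count as showing that an app works.

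Each level has its own cost. If the analysis section is followed, six pairwise tests at 0.05 inflate the chance of a false positive. If 0.008 is carried into the analysis as a flat threshold, error is controlled, but by a single-step rule that a step-down on the same six p-values beats at the same family-wise 5%.

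Interpretation is also at stake. A trial in which one app beats another, but none beats control, would have the same formal standing as one in which an app beats control.

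**Working it through.** **1. Where 0.008 comes from.** Four groups give 4 × 3 / 2 = 6 pairs, and 0.05/6 = 0.0083. Three app-versus-control contrasts would give 0.05/3 = 0.0167, which does not fit. The six-pair reading is therefore an inference, but the only natural one.

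**2. The plan's own figure.** For two means, n = 2·SD²·(z₁₋α/₂ + z₁₋β)² / Δ². Take Δ = 0.07, SD = 0.11 (the smaller quoted SD; the article does not say which was used) and power 0.90.

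- α = 0.05/6: 2 × 0.0121 × (2.638 + 1.282)² / 0.0049 = 75.9, so 76.
- α = 0.008: 2 × 0.0121 × (2.652 + 1.282)² / 0.0049 = 76.4, so 77.

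The stated 76 is reproduced at 0.05/6, but before dropout. With 25% dropout it becomes 76/0.75 = 101.3, so 102.

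**3. Following the analysis section: all tests at 0.05.** Six independent tests would give 1 − 0.95⁶ = 26.5%. The six pairs share arms, and simulation with that correlation gives about 20% under the global null. For the three app-versus-control tests alone it is about 12.5%.

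**4. Following the sizing section: flat 0.008 or 0.05/6.** Simulated family-wise error under the global null is about 4%. The rule is valid.

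**5. Step-down on the same six p-values.** Sort them from smallest to largest and stop at the first failure.

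- Holm: divisors 6, 5, 4, 3, 2, 1.
- Shaffer: divisors 6, 3, 3, 3, 2, 1. With four groups, once one equality is false at most three of the others can still be true.

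Both reject everything that the flat rule rejects, so no contrast loses power. Simulated error under the global null stays at about 4.1%.

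**6. Size of the gain.** Assumptions: 320/4 = 80 per arm, less 25% = 60 completers; t tests on all six pairs; all three apps equally effective. As a check on the flat rule, 0.07 / (0.11·√(2/60)) = 3.49, and 3.49 − 2.64 = 0.85. The normal approximation then gives Φ(0.85) = 0.80; the t test gives about 0.79.

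| Scenario | Flat 0.05/6 | Holm | Shaffer |
|---|---|---|---|
| +0.07, SD 0.11: power per app-versus-control contrast | 79% | 82% | 84% |
| +0.07, SD 0.11: all three shown | 59% | 65% | 70% |
| +0.05, SD 0.11: per contrast | 43% | 45% | 49% |
| +0.07, SD 0.155: per contrast | 42% | 45% | 48% |

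SD 0.155 is the root mean square of 0.11 and 0.19. The figure of 0.05 is the upper end of the quoted minimal important difference.

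**7. The interpretive gap.** With one truly effective app (+0.07, SD 0.11, 60 completers), the flat rule gives a significant app-versus-app result with no app beating control in about 15% of trials.

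**8. Testing app versus control first, with app versus app behind a gate.** Same n and SD, Holm at 0.05 within each family:

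- Gate opens on any control success: family-wise error 7.1% with one effective app, 8.1% with two, and up to about 9.8% with large effects.
- Gate opens only when all three succeed: error is about 5% or less, but with one effective app the power to show that it beats another app falls from about 79% to 0.4%.

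**The case against.** The strongest reply is that 0.008 is only a sizing level and that no part of the article describes a six-pair Bonferroni analysis. This stands in part. A reader might infer that the plan as written loses power to a flat correction, but the written analysis rule is 0.05, so taken literally the fault is inflated error. The power loss arises only if 0.008 is carried into the analysis.

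A second reply is that testing order belongs in a statistical analysis plan, which is not shown. The absence of an order would indeed be no finding. Two conflicting levels within one article are, and the flat 0.008 is a choice made there.

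A reader might also infer that app versus control is plainly primary and app versus app an afterthought. The article does not support that. The abstract sets out to evaluate and compare the three systems, the background says that all four groups will be compared, and the Discussion's phrasing ranks nothing. Only the words opening the conclusion's sentence hint at an order, and the same conclusion hopes to identify the best app. This is why a gate cannot be recommended as a free improvement: it either exceeds 5% or almost removes a stated aim.

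Finally, a step-down over six pairs does not by itself say what counts as efficacy. That is correct, and it needs its own sentence.

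**Conclusion.** The point holds in a limited form. The sizing level (0.008) and the analysis level (0.05) conflict, and no EQ-5D contrast is named as deciding efficacy. Under the analysis section as written, family-wise error over six pairs is about 20% under the global null. Under a flat 0.008 it is controlled, and the flat rule is valid but inefficient. A step-down would add about 3 points (Holm) or 5 points (Shaffer) of power per app-versus-control contrast, and about 6 or 11 points for showing all three.

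These gains rest on 60 completers per arm, SD 0.11 and equal effects of 0.07, and on the inference that 0.008 means 0.05/6. They are modest. The step-down should not be read as a repair of the trial's power: 76 per group reproduces only before the stated dropout, and with SD 0.155 power per contrast stays below 50% under either step-down. That shortfall is a separate matter.

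**What to change.** 1. In Statistical analysis, replace the blanket P < 0.05 for the primary endpoint with a Holm or Shaffer step-down over the six pairwise EQ-5D p-values at two-sided family-wise 5%. For Shaffer: the smallest p against 0.05/6, the next three against 0.05/3, then 0.05/2, then 0.05, stopping at the first failure.
2. State that efficacy is claimed only for an app that beats control. App-versus-app results answer the comparative question and do not establish efficacy on their own.
3. In Sample size calculation, say that 0.008 is 0.05/6 for the six pairs and is the first-step level of that procedure, so that the two sections agree.

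The cost is a few sentences, with no extra patients or data. No contrast loses power relative to flat 0.008. The one loss is that step-down procedures do not give the simple simultaneous confidence intervals that a single-step Bonferroni does. Recruitment has started, so the rule should be fixed before outcomes are compared by group. A gate that puts app versus control first is not recommended, for the reasons in the working.

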**Methods:**

This single center randomized controlled study is designed to evaluate the efficacy of digital healthcare applications for lung cancer patients after thoracoscopic lung resection. A total of 320 patients will be enrolled and randomized 1:1:1:1 into four different groups, with one group each using the smartphone applications NOOM, Walkon, and Efilcare and the fourth being the control group without intervention. Questionnaires will be administered to patients at baseline and after 3, 6, and 12 months. The primary endpoint will be the score on the EuroQol five-dimension index. Secondary endpoints will include other questionnaires about quality of life and dyspnea.

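### The 76 per group matches a pre-dropout requirement with SD 0.11; with 25% dropout, 320 patients give about 78% power (less with the other cited SD), not 90%

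*Protocol article*

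**What the plan says.** The design rests on the assumption that "effective postoperative rehabilitation could restore the quality of life to a similar level before surgery". The figures come from one earlier study, in which "the preoperative and postoperative EQ-5D indices were 0.81 ± 0.19 and 0.74 ± 0.11, respectively". The error rate is divided for the four arms: "Because patients were classified into four groups, the margin of type 1 error was set at 0.008". The result is "Calculations showed that a minimum of 76 patients in each group was required to detect a significant difference at the 0.008 level", and the same sentence continues "with a power of 0.9 and a dropout rate of 25" per cent.

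The abstract fixes the size: "A total of 320 patients will be enrolled and randomized 1:1:1:1 into four different groups", which is 80 per group. The Statistical analysis section says "All tests of significance will be two-sided" and names Student's t-test or the Mann–Whitney test for continuous variables.

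The sample size section does not say which of the two SDs entered the formula, or whether 76 is the number before or after allowance for dropout.

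**The concern.** The article gives every input of a standard two-group calculation and also its result, so the two can be compared. They do not agree once the stated dropout is included.

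This is the only justification given for the size of the trial on its primary endpoint. If the results are read against a claim of 90% power, a non-significant comparison will look like fairly strong evidence that an app does not restore quality of life. The planned chance of missing the assumed effect is 10%. At 60 evaluable per group it is about 22% with the more favourable SD and about 59% with the two cited SDs together.

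**Working it through.** **Inputs**

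- Difference: 0.81 − 0.74 = 0.07 (Sample size calculation).
- SDs: 0.19 and 0.11 (same section). Taken together, √((0.19² + 0.11²)/2) = 0.155.
- Alpha: 0.008 (same section). It is apparently 0.05/6 = 0.00833, for six pairwise comparisons of four groups.
- Two-sided tests (Statistical analysis).
- Power 0.90 and dropout 25% (Sample size calculation).
- Enrolment: 320 in four equal groups (abstract), so 80 per group and 80 × 0.75 = 60 evaluable.

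**Reproducing 76**

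n per group = (z₁₋α/₂ + z₀.₉₀)² × (SD₁² + SD₂²) / 0.07²

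- At 0.008: (2.652 + 1.282)² = 15.47. With SD 0.11 in both groups, 15.47 × 0.0242 / 0.0049 = 76.4.
- At 0.05/6: (2.638 + 1.282)² = 15.36. With SD 0.11 in both groups, 15.36 × 0.0242 / 0.0049 = 75.9, which rounds up to 76.

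So 76 is the evaluable number for SD 0.11, before dropout. The t-based requirement is 78 to 79, so the small gap to 76 is only the normal approximation.

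**Adding the stated dropout**

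| SDs | Evaluable per group | Divided by 0.75 | Total |
|---|---|---|---|
| 0.11 in both | 76 (at 0.05/6) to 77 (at 0.008) | 102 to 103 | 408 to 412 |
| 0.19 and 0.11 | 15.47 × 0.0482 / 0.0049 = 152.2 | 203 (204 if 153 is inflated) | 812 to 816 |
| 0.19 in both | 15.47 × 0.0722 / 0.0049 = 228.0 | 304 | 1,216 |

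Multiplying by 1.25 instead of dividing by 0.75 still gives 95.5 per group in the most favourable row. No SD in the section gives 76 with dropout included. If 76 evaluable are required, the planned 80 per group allow for a loss of 4/80 = 5%, not 25%.

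**Power delivered** (noncentral t, two-sided 0.008, difference 0.07)

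| Evaluable per group | SD 0.11 | SDs 0.19 and 0.11 | SD 0.19 |
|---|---|---|---|
| 57 (76 enrolled, 25% lost) | 0.76 | 0.39 | 0.24 |
| 60 (80 enrolled, 25% lost) | 0.78 | 0.41 | 0.25 |
| 76 | 0.89 | 0.54 | 0.34 |
| 80 (no loss) | 0.91 | 0.57 | 0.36 |

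**Difference detectable with 90% power at 60 per group**

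3.934 × SD × √(2/60), where 3.934 = 2.652 + 1.282 before rounding:

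- SD 0.11: 0.079.
- SDs 0.19 and 0.11: 0.111.

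The t-based values are 0.080 and 0.113. For 60 per group to give 90% power at 0.07, the common SD would have to be about 0.096, below both cited values.

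**The case against.** The best defence starts from the fact that 76 comes out of an ordinary two-sample formula with inputs in the section. A reader might infer that the number cannot be reproduced at all. That is not so; what fails is the claim that it already covers 25% dropout.

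Nor does the document support leading with 41%, or calling the trial a coin-flip. The section never says that the two SDs were combined. The value 0.11 is the postoperative SD, follow-up in every arm is postoperative, and 0.11 is the SD that yields 76. Under it the shortfall is about 12 points. The lower figures belong in the range as sensitivity values.

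A reader may also notice that 76 is half of 152, and suspect that a paired or one-sample formula was used. The section describes no such test, and the SD 0.11 route explains 76 more simply. That diagnosis is speculation.

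Two further points limit the claim without removing it:

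- **Threshold.** The Statistical analysis section uses P < 0.05. At that level, 60 per group give 0.93 with SD 0.11 and 0.69 with both SDs, without control for six comparisons. But the power statement is made explicitly for 0.008.
- **Baseline adjustment.** EQ-5D is measured at baseline. With a baseline correlation of 0.5 (an assumption; the article gives none), the SD falls by a factor of √(1 − 0.25), and power with SD 0.11 would be about 0.90. So 78% is not an absolute ceiling. However, the article names only unadjusted tests, and its calculation gives no correlation.

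Finally, this is not detail left to a fuller document. The inputs and the result are both printed, and they disagree.

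**Conclusion.** The point holds in this form: 76 is a pre-dropout number based on the smaller cited SD, and the statement that it gives 90% power with 25% dropout is wrong under every SD in the section. With 320 enrolled and 60 evaluable per group, power for 0.07 is about 78% with SD 0.11, 41% with SDs 0.19 and 0.11, and 25% with SD 0.19.

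These figures assume an unadjusted two-sided t-test between two groups at 0.008, and dropout of exactly 25% in each group. That SD 0.11 was used is inferred from the match with 76; the article does not say so. The arithmetic is certain given the inputs. How large the shortfall is depends on the SD, so it should be reported as a range. The statement needs correction because it is the stated basis for the size of the trial.

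**What to change.** Keep 320 and rewrite the last sentence of the sample size section so that it names the SD used, says that 76 is the evaluable number before dropout, and gives the power the design delivers. For example:

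> With SD 0.11 in both groups, 76 evaluable patients per group are required before allowance for dropout. With 80 randomised and about 60 evaluable per group, power to detect 0.07 at two-sided 0.008 is about 0.78 (SD 0.11 in both groups), falling to about 0.41 if the SDs are 0.19 and 0.11. The difference detectable with 90% power is about 0.08 to 0.11.

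If a different SD or formula was in fact used, state it and recompute these figures from it. The cost is one corrected paragraph and a less favourable stated power. No extra patients and no change in conduct are needed.

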## Methods/design

### Study design

This study is designed as a single center randomized controlled study evaluating the efficacy of digital healthcare applications for lung cancer patients who undergo thoracoscopic lobectomy. Patients will be recruited at Asan Medical Center, a university affiliated 2700-bed tertiary medical center. A total of 320 patients will be enrolled. The study duration is 1 year, and all enrolled patients will be evaluated at outpatient clinics by attending clinicians at baseline and at 3, 6, and 12 months after surgery. The study protocol has been approved by the Institutional Review Board of Asan Medical Center (IRB no. 2020-1015), and written informed consent will be obtained from all participants by attending investigators and research assistants.

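### Unadjusted two-sample tests are named for a four-visit EQ-5D outcome with 25% expected dropout; a baseline-adjusted repeated-measures model would be more precise and less exposed to dropout that differs by arm

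*Protocol article*

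**What the plan says.** Under Study design, patients are assessed "at baseline and at 3, 6, and 12 months after surgery", and Table 1 places the questionnaires at all four time points. Data collection and study outcome makes the EQ-5D index the primary endpoint and names no visit.

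Sample size calculation takes its planning values from a study in which "the preoperative and postoperative EQ-5D indices were 0.81 ± 0.19 and 0.74 ± 0.11, respectively". It states that "the margin of type 1 error was set at 0.008" and that "a minimum of 76 patients in each group was required", "with a power of 0.9 and a dropout rate of 25" per cent. Study design adds: "A total of 320 patients will be enrolled".

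Statistical analysis says that continuous variables are given as mean and standard deviation or as "median [interquartile range] and compared by Student’s *t*-test or the Mann–Whitney U-test". It adds: "All tests of significance will be two-sided". It names no other method for a continuous outcome.

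**The concern.** The EQ-5D index is continuous, so the named tests cover the primary endpoint. A two-sample test cannot take four repeated measurements together. It has to be applied to one visit, or to one change score, at a time. The article does not say that testing is done visit by visit, but the named tests leave little else.

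This has two consequences at a later visit:

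- **Precision.** If the visit's score is compared directly, baseline EQ-5D is ignored although every patient has it.
- **Dropout.** Only attenders enter the comparison, and leavers' month-3 or month-6 scores do not inform it. If leaving depends on earlier EQ-5D, and does so differently between arms, the difference among attenders is biased. An arm that loses its poorer patients looks better than it is. Three arms use apps with different demands and the fourth uses none, so different reasons for leaving are plausible. The article does not document them.

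**Working it through.** **1. The plan's own figure.** Per group, n = 2(z₁₋α/₂ + z₀.₉)² SD²/Δ², with Δ = 0.81 − 0.74 = 0.07. The article does not say which SD was used. With SD 0.11 and two-sided α = 0.008: 2 × (2.652 + 1.282)² × 0.0121/0.0049 = 76.4, so 77; with α = 0.05/6 it is 76. With SD 0.19 it is 228. So 76 is obtained as a number analysed, before dropout. Whether it allows for the 25% is a separate question. Here it shows only that the design rests on a plain two-sample comparison of means.

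**2. Attenders at month 12.** 320/4 = 80 per arm; 80 × 0.75 = 60 if all loss occurs by then. About 4 × 20 = 80 of 320 patients are then absent from that test.

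**3. Variance of an arm mean at month 12** (in units of SD²/n randomised). Assumptions: equal correlation ρ between all visits, and cumulative dropout of 10%, 18% and 25% at months 3, 6 and 12.

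- Complete-case t-test: 1/0.75 = 1.333.
- Complete-case analysis adjusted for baseline: (1 − ρ²)/0.75.
- Mixed model with baseline: (1 − ρ²) × [(1 − b)/0.75 + (b − r²)/0.82 + r²/0.90], where r = ρ/(1 + ρ) and b = 2r²/(1 + r).

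| ρ | t-test | Baseline-adjusted, complete cases | Mixed model | Reduction, mixed model vs t-test | Of which beyond baseline adjustment |
|---|---|---|---|---|---|
| 0.4 | 1.333 | 1.120 | 1.100 | 17.5% | 1 − 1.100/1.120 = 1.8% |
| 0.5 | 1.333 | 1.000 | 0.977 | 26.7% | 1 − 0.977/1.000 = 2.3% |
| 0.6 | 1.333 | 0.853 | 0.829 | 37.8% | 1 − 0.829/0.853 = 2.8% |

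The last column is relative to the baseline-adjusted complete-case variance. Baseline adjustment alone gives 16%, 25% and 36%.

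**4. Bias by hand.** Suppose 25% leave one arm with month-3 scores 0.5 SD below that arm's mean, the month-3 to month-12 correlation is 0.6, and the other arm loses patients at random. The attenders' month-12 mean shifts by 0.6 × 0.25 × 0.5/0.75 = 0.10 SD. With the root mean square of the two quoted SDs, √[(0.19² + 0.11²)/2] = 0.155, this is 0.0155: 22% of 0.07 and about half of 0.03, the lower end of the article's range for a minimal clinically important difference. With SD 0.11 or 0.19 the shift is 0.011 or 0.019.

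**5. Bias by simulation.** Two arms of 80, four visits, SD 0.15, about 25% monotone dropout by month 12, correlation 0.3 to 0.7, 2,000 runs per scenario. Where leaving depends on a score, the log-odds change by 1 per SD. Monte Carlo error is about 0.027/√2000 = 0.0006.

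| Dropout depends on | Attenders only: bias | Mixed model: bias |
|---|---|---|
| Nothing (random) | none | none |
| Earlier score, same in both arms | none | none |
| Earlier score, one arm only | +0.011 to +0.025 | within 0.001 |
| Earlier score, opposite in the two arms | −0.023 to −0.050 | within 0.001 |
| Unseen current score, one arm only | +0.020 to +0.030 | +0.009 to +0.015 |

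Under random dropout the simulated mixed model lowered the standard error by only about 1% to 7% (0.0275 to 0.0273 at ρ = 0.3; 0.0275 to 0.0255 at ρ = 0.7). A repeated-measures model without baseline adjustment gives gains of that order, which again places most of the gain in step 3 with baseline.

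**The case against.** The strongest objection is that an article condenses the plan, and that longitudinal modelling and missing-data handling normally sit in an analysis plan that is not shown. That stands for anything the article leaves out, and the absence of a missing-data method is not the point here. But the article does name the tests for continuous outcomes, and that stated choice can be improved on.

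Other parts of the objection stand and limit the point:

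- A reader might infer that leavers' data are thrown away. They are not: a month-3 score still counts in a month-3 test. It is lost only to later comparisons.
- A reader might infer that the trial's result will be biased towards the apps. The article does not support that. Bias in the difference needs a link between score and leaving that differs by arm, and this is an assumption. All arms share the same clinic visits with CT, laboratory and lung-function tests, so attendance does not hang on app use alone.
- A reader might credit the 18% to 38% to the use of intermediate visits. Nearly all of it is baseline adjustment, which a simple covariance analysis would also give.
- A reader might take the mixed model as a cure for dropout. It is not one when leaving depends on scores never observed, and patients with no post-baseline score contribute nothing to it.
- The size depends on the primary visit, which is not named. At month 3, with monotone dropout, the model is essentially a baseline-adjusted covariance analysis, and its dropout advantage over that analysis disappears.

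**Conclusion.** The point holds in this limited form. For the primary outcome the article names unadjusted two-sample tests, when data already being collected support a better analysis.

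The firmer gain is precision, from using baseline. It rests on assumed correlations and an assumed dropout pattern, and on comparison with an unadjusted test of the visit score.

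Protection against bias is conditional. It is worth about 0.01 to 0.025 on EQ-5D if dropout tracks earlier scores in one arm only, more if the links run in opposite directions, and nothing if they are the same. Against a planned difference of 0.07, 0.011 to 0.025 is about 16% to 36%. The change should be made, but the article gives no ground for saying that the result will be biased or in which direction.

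**What to change.** For EQ-5D, replace the two-sample tests with one mixed model for repeated measures:

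- Terms: group, visit, group-by-visit, baseline-by-visit, sex and FEV1 stratum.
- Unstructured covariance; patients analysed in the arm allocated.
- Group contrasts read at one primary visit, named before the data are analysed.
- One delta-adjusted sensitivity analysis, in which the missing scores of patients lost from the app arms are made progressively worse, because the model does not cover dropout tied to unobserved scores.

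The cost is slightly more analysis work. SAS and R are already named, sex and FEV1 are already stratification factors, and no new data or visits are needed.
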